### Ethical considerations

Full ethics approval was given by the Northern Y Ethics Committee in January 2011 (NTY 10/11/090). Consent was obtained for facility participation rather than individual resident participation, as no identifying data is being collected and none of the interventions will be outside the usual clinical practice provided by facility staff. Only National Health Index (NHI) numbers (a national healthcare identification number for each person in New Zealand) were collected by the researchers. All individual residents’ information was kept anonymous to the researchers.

### Intervention

The intervention builds on aged care programmes already in place in the three Auckland region DHBs. Each DHB has gerontology clinical nurse specialists (GNSs) providing outreach to facilities, but the models of care vary between the DHBs and there is no consistent method to Identify high-risk facilities. The trial intervention delivers outreach tailored to facility needs. The multi-disciplinary team is considered a critical element
[25]. These teams were established at each of the three Auckland DHBs, building on existing RAC outreach services. The team comprises the facility General Medical Practitioner and Nurse Manager, a DHB geriatrician, a DHB Gerontology Nurse Specialist and a community pharmacist that services the facility or DHB clinical pharmacist.

The interventions in this study include:

• Initial baseline facility assessment to identify areas of need and facility care plan

• Benchmarking monitoring resident quality indicators that are linked to the quality of care provided (falls, nutrition, use of restraints, weight loss, UTIs, residents on nine or more medications).

• Three one-hour multi-disciplinary team (MDT) meetings to be held monthly for the first three months at each intervention facility, including medication reviews by the geriatrician in conjunction with the GP, pharmacist and nurse manager. At most, six residents were considered at each meeting with new admissions, those recently hospitalised, and those residents on nine or more medications given priority.

• Gerontology education and clinical coaching for RAC nurses and caregivers including advanced care planning for end-of-life care, nutrition and hydration, early identification of illness, falls prevention, end-stage dementia care, communication with families and practical aspects concerned with resident care.

The intervention continued for nine months with the intensity of the intervention decreasing over time to foster facility independence prior to the conclusion of active involvement, including months 6 and 8 where facilities did not receive any input by the GNSs. The GNSs began the intervention with one new facility per month in order to allow sufficient time for the organisation and delivery of the intervention.

Facilities provided monthly lists of all residents showing only residents’ unique identifiers, care type, and admission and discharge dates, to facilitate tracking residents and for sub-group analyses. The data for all acute hospitalisations and deaths will be retrieved from the Ministry of Health’s routinely collected public hospital admissions data on presentation of the unique identifier.

### Outcome measures

The primary outcome measurements comprise:

 1. Rate of ASH admissions classified using a pre-determined set of ICD codes.

 2. Number of acute admission hospital days.

 3. Number of deaths from any cause, including death in acute hospital or elsewhere obtained from a national mortality database.

Numbers and rates for these three outcomes will be calculated as the proportion of residents hospitalised (1), number of hospital days per occupied bed per year (2) and deaths per person-year (3). Sub-group analyses will be conducted, by age group and gender, and by facility type.

This data will be collected from the date of randomisation to 14 months after the first visit by the GNS in the intervention arm, and for the paired facility in the control arm. Hospitalisation records will be sought five months after the final facility completes its intervention, in order to allow for any delays in registering admissions. Paper reports from each participating facility will enable checking against national records.

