## Methods/design

This is a randomised controlled trial of a complex intervention of a package of supports and services provided by District Health Boards (DHBs) interdisciplinary team outreach to RAC facilities.

The study is taking place in the greater Auckland area of New Zealand. Auckland is the largest metropolitan area of New Zealand with a population of 1.4 million people. Within this region there are 175 aged care facilities, from which the participating facilities were selected on the basis of higher than ‘expected’ hospital admission rates. A total sample size of 1400 resident-years was originally anticipated to provide 80% power (5% significance) to detect a 25% reduction in rate of ASH hospitalisations in the intervention group compared to the control group when an event rate of 60 events per 100 years was expected. However, observed event rate in another cohort after commencement of the trial showed a lower event rate, so power estimates were recalculated. With 18 facilities for each group each with 14 months of follow-up, an average of 38 beds per facility and bed occupancy of 90%, we expect a total of 1500 resident years of follow-up. Revised power is estimated at 53%, considering:

• Inflated sample size as the design effect of 2.0 will allow for moderate intracluster correlation for hospitalisation rates of 0.025
[23,24]

• Rate of 35 ASH admissions per 100 resident years in control facilities vs. 26 ASH admissions in intervention facilities, assuming a Poisson distribution where the mean equals the variance. The control event rate was estimated from re-analysis of the RACIP study (Boyd et al., 2008) and the OPAL study cohort (results not yet published).

However, we anticipate an improvement in power because;

• the facilities were chosen (from statistical modelling) for their higher event rates (e.g. an event rate of 0.40 would provide power of 0.67)

• short-stay residents (under-represented in OPAL-based rates) have a higher event rate

• adjustment for covariates in our analysis will reduce confidence intervals around effect size

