### Analyses

Analysis of primary endpoints will compare rate of ASH admissions between treatment groups followed by other main endpoints. Simple unadjusted rates, relative risks and 95% confidence intervals will be obtained initially, with subsequent multiple regression analysis adjusting for paired randomisation and other variables. Negative binomial regression will be used. Baseline rates will likely be included as a covariate in regression models as pre-intervention hospitalisation rates will be highly predictive of post-intervention rates.

Sub-group analyses to check for effects that differ from the overall treatment effect will be performed for the following:

• facilities classed as charitable, religious or welfare facilities vs. for “for profit” facilities

• for facilities that have only rest-home beds vs. those with both rest-home and hospital beds

• for long-stay vs. short-term (e.g. respite or palliative care) residents

• for facilities providing after-hours primary care cover through either their usual GP or a contracted after-hours primary care provider, vs. those without such cover (effectively using ambulance and emergency department for after-hours primary care)

All main analyses will be formally analysed on an "intention to treat" basis. Tests of significance will be two-tailed. Analysis of secondary outcomes will use standard statistical procedures applicable to categorical, continuous, or failure-time data as appropriate.

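### The calculation rule for the first-listed primary outcome (a proportion of residents) contradicts the admission rate that the protocol names, powers and compares

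*Protocol article*

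**What the plan says.** Outcome measures lists three primary outcomes. The first is "Rate of ASH admissions classified using a pre-determined set of ICD codes". The sentence that then says how each is to be computed begins "Numbers and rates for these three outcomes will be calculated as the proportion of residents hospitalised (1"; the closing number ties that clause to the first outcome. The same sentence gives the other two an exposure denominator: "number of hospital days per occupied bed per year (2) and deaths per person-year (3".

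Two other sections treat the first outcome as a rate:

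- Methods/design states the original target as "80% power (5% significance) to detect a 25% reduction in rate of ASH hospitalisations". The revised calculation rests on "Rate of 35 ASH admissions per 100 resident years in control facilities vs. 26 ASH admissions in intervention facilities", with Poisson counts.
- Analyses says "Analysis of primary endpoints will compare rate of ASH admissions between treatment groups followed by other main endpoints", and "Negative binomial regression will be used".

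The text following the Intervention section says that facilities supply monthly resident lists with entry and exit dates, so time at risk can be computed for each resident.

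**The concern.** An admission rate and the share of residents admitted at least once are different quantities. The rate counts every admission and divides by time at risk. The share counts a resident once, however many admissions follow, and takes no account of how long that resident was observed.

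The difference matters here because residents come and go. Short-stay residents are included and are said in Methods/design to have a higher event rate, and death is itself a primary outcome. A share of residents therefore depends on length of stay and survival as well as on the admission rate.

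This is not a detail left for an analysis plan. The article states a computation rule, and that rule disagrees with the outcome's own name, with the basis of the power calculation and with the planned comparison. At stake is which number is the first primary result, and whether the quoted power refers to it.

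**Working it through.** **1. The passages side by side**

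| Place | Quantity for outcome 1 |
|---|---|
| Outcome measures, list | rate of ASH admissions |
| Outcome measures, calculation sentence | share of residents admitted; no time denominator |
| Methods/design, power | ASH admissions per 100 resident-years, Poisson |
| Analyses | rate of ASH admissions; negative binomial (a count model) |

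The calculation sentence is the one that differs. Analyses also asks for unadjusted rates and relative risks, so that wording alone does not settle the scale.

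**2. Which scale the power figures are on**

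Inputs from Methods/design: design effect 2.0, two equal groups, 5% significance (two-tailed, from Analyses). Effective exposure per arm is n = resident-years / 2 / 2.0. For a Poisson rate comparison, power = Φ[(r0 − r1)/√((r0 + r1)/n) − 1.96].

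- Original: 1400 resident-years, 0.60 vs 0.45, n = 350. 0.15/√(1.05/350) = 2.739, power 78% (stated 80%).
- Higher rate: 1500 resident-years, 0.40 vs 0.40 × 26/35 = 0.297, n = 375. Power 66.5% (stated 67%).
- Revised: 0.35 vs 0.26, n = 375. 0.09/√(0.61/375) = 2.231, power 60.7% (stated 53%).

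Two of the three figures reproduce closely as rate comparisons. The 53% does not follow from its stated inputs, which is a separate matter. Reading 0.35 and 0.26 as proportions does not rescue it: 0.09/√((0.35×0.65 + 0.26×0.74)/375) = 2.69, power about 77%.

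**3. What the proportion would show under the planned effect**

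Assumption: mean time at risk T = 1500/1700 = 0.882 year, the same for every resident (1700 from the Abstract, 1500 from Methods/design). Planned rate ratio: 0.26/0.35 = 0.743.

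- Poisson: share admitted = 1 − exp(−rT).
- Negative binomial with dispersion k (assumed): share = 1 − (1 + k r T)^(−1/k).
- Control admissions uncounted = 1 − share/(0.35 × 0.882) = 1 − share/0.309.

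| | Control | Intervention | Risk ratio | Uncounted |
|---|---|---|---|---|
| Poisson | 26.6% | 20.5% | 0.77 | 14% |
| k = 1 | 23.6% | 18.7% | 0.79 | 24% |
| k = 2 | 21.4% | 17.2% | 0.80 | 31% |

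**4. Power, compared like for like**

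Effective residents per arm: 1700/2/2.0 = 425. For the share, power = Φ[(p0 − p1)/√((p0(1−p0) + p1(1−p1))/425) − 1.96]. For the rate, the variance per arm is (r/T + k r²)/425.

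| | Share of residents | Admission rate |
|---|---|---|
| Poisson | 55% | 61% |
| k = 1 | 42% | 51% |
| k = 2 | 34% | 43% |

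Clustering within residents lowers power on either scale. The loss due to using the share is about 6 to 10 percentage points. The same design effect is assumed for both scales.

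**5. Unequal time at risk**

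With the same rate of 0.35 in both arms and Poisson counts, assumed mean times of 0.88 and 0.95 year give shares of 26.5% and 28.3%; 0.88 and 1.00 year give 26.5% and 29.5%. The arm observed longer shows more residents admitted with no difference in rate. These times are illustrations only.

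**The case against.** The best reply is that one clause stands against the rest of the article. The outcome's name, both power statements and the Analyses section all point to a rate, and even the disputed sentence begins by promising numbers and rates. It may be a drafting slip or a loose descriptive summary. That stands: the document contradicts itself, and does not consistently adopt a proportion. The conflict remains, however, because the clause is the only stated computation rule for this outcome and it is numbered to it.

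Several stronger readings are tempting and are not supported:

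- **That the trial will be analysed on a proportion.** Analyses keeps the rate comparison. The harm arises only if the clause is followed over that section.
- **That the restriction to ASH diagnoses has been dropped.** The clause does not repeat it, but its number points back to an outcome defined by ICD codes.
- **That the sole primary outcome lacks a time denominator.** All three outcomes are listed as primary; this is the first of them.
- **That a definite bias from unequal stay can be quoted.** The document gives neither the spread of stay nor any difference between arms, so a figure would rest on invented stays.
- **That 53% was computed for the proportion, since 55% is close.** The text gives its inputs per 100 resident-years with Poisson counts, so the nearness is no evidence of a different scale.

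The 0.88 year is also soft. The article does not say that 1700 counts everyone ever resident, and 36 × 38 × 0.9 × 14/12 gives 1436 resident-years, not 1500.

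**Conclusion.** The point holds as an internal contradiction in the definition of a primary outcome. The calculation clause for the first-listed outcome is wrong as written: it conflicts with the outcome's name, the power basis and the planned comparison, and nothing in the article resolves it.

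If the clause were followed under the planned effect, the treatment contrast would move modestly towards the null, from a rate ratio of 0.743 to a risk ratio of about 0.77 (Poisson) or 0.79 to 0.80 (assumed dispersion 1 to 2). This rests on a common 0.88 year at risk, which is an assumption. The stated power would not describe that analysis. Bias from stay or survival differing between arms is possible, and its direction follows from the arithmetic, but its size cannot be taken from the document.

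The shift is not dramatic. The point needs correcting because the protocol currently permits two different first primary results.

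**What to change.** Change only clause (1) of the calculation sentence in Outcome measures, to: number of ASH admissions, including repeat admissions, per resident-year.

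In Analyses, state that this count enters the planned negative binomial model with log resident-years as an offset, and that the effect is reported as a rate ratio with its 95% confidence interval. The proportion of residents with at least one ASH admission may be reported as a descriptive figure. Leave outcomes (2) and (3) as written; no fault has been shown in either.

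The cost is one clause and one clarifying sentence. The entry and exit dates needed for resident-years are already collected. The change should be made and dated before outcome data are compared between arms.

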**Outcomes:**

Hospitalisations are recorded from routinely-collected acute admissions during the 9-month intervention period followed by a 5-month follow-up period. ICD diagnosis codes are used in a pre-specified definition of potentially reducible admissions.

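### For the last-starting facilities and their paired controls, the five months allowed for late registration are the same five months as follow-up, so the allowance there is zero

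*Protocol article*

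**What the plan says.** Three sections of the protocol article fix the timing.

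- **Length of the intervention.** The Intervention section says: "The intervention continued for nine months with the intensity of the intervention decreasing over time". The Outcomes paragraph of the Abstract counts admissions "during the 9-month intervention period followed by a 5-month follow-up period".
- **End of outcome counting.** The Outcome measures section sets this collection window: "from the date of randomisation to 14 months after the first visit by the GNS in the intervention arm, and for the paired facility". The last words refer to the matched control. The power paragraph in Methods/design uses the same length: "With 18 facilities for each group each with 14 months of follow-up".
- **Extraction date.** The Outcome measures section then says: "Hospitalisation records will be sought five months after the final facility completes its intervention, in order to allow for any delays in registering admissions".

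Two further statements matter. Starts are staggered: "The GNSs began the intervention with one new facility per month". And paper reports from the facilities are to be used as a check on the national records.

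**The concern.** The extraction sentence gives its own purpose, which is to leave time for late registration. But the five months it names begin when the intervention ends, and that same interval is already used as the follow-up period. For the facilities that start last, nothing is left over for registration.

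The lead primary outcome is the rate of ambulatory sensitive (ASH) admissions, identified by ICD code. An admission that is not yet registered and coded at extraction cannot be counted. The resident-time behind it comes from the monthly facility lists and stays in the denominator. The loss falls at the end of late starters' windows, in months 10 to 14, after the active intervention has stopped. It lowers the absolute rates, removes events from a trial whose revised power is given as 53%, and makes late-starting facilities look quieter than they were for reasons unrelated to treatment.

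**Working it through.** **Inputs from the protocol article:** intervention 9 months (Abstract; Intervention); follow-up after it 5 months (Abstract); outcome window to month 14 from the first GNS visit (Outcome measures); extraction 5 months after the final facility completes its intervention (Outcome measures); 18 facilities per arm and power 53% (Methods/design).

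**Step 1: reproduce the window.** 9 + 5 = 14 months, which matches the stated figure.

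**Step 2: lag for the last starter.** Extraction falls at 9 + 5 = month 14 after its first visit. Lag = 14 − 14 = 0 months. The paired control shares the window, so its lag is also 0. This takes the first visit as the start of the nine months. The first listed element of the intervention supports that: "Initial baseline facility assessment to identify areas of need and facility care plan". Any gap between first visit and start of intervention would give a lag equal to that gap.

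**Step 3: lag for the others.** A facility that starts s months before the last one has a lag of s months.

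**Step 4: possible size.** The article gives neither a registration delay nor the number of GNSs, so both are assumed. Suppose every admission in the last L months before extraction is missing. A facility with lag s then loses max(L − s, 0) months, and one sequence of monthly starts loses L + (L − 1) + … + 1 facility-months, provided it contains at least L facilities. The intervention arm has 18 × 14 = 252 facility-months.

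| Assumed L | Lost per sequence | One sequence of 18 | Three sequences of 6 |
|---|---|---|---|
| 1 month | 1 | 1/252 = 0.4% | 3/252 = 1.2% |
| 2 months | 3 | 3/252 = 1.2% | 9/252 = 3.6% |
| 3 months | 6 | 6/252 = 2.4% | 18/252 = 7.1% |

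More sequences compress the starts: six sequences of three facilities with L = 3 would lose 6 × 6 = 36 of 252 (14.3%). For a last-starting facility on its own the loss is L/14, or 7% to 21% for L of 1 to 3. The paired controls lose the same amounts.

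**Step 5: effect on power.** Power of 53% corresponds to a standardised effect of 1.960 + 0.075 = 2.035.

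- Losing 7.1% of the information: 2.035 × √(1 − 0.071) = 1.961, and 1.961 − 1.960 ≈ 0, so power is about 50%.
- Losing 2.4%: 2.035 × √(1 − 0.024) = 2.011, and 2.011 − 1.960 = 0.051, so power is about 52%.

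**Step 6: the alternative reference point.** Five months after the final pair's month 14 is month 19. The lag is then 19 − 14 = 5 months for the last starters and longer for all others.

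**The case against.** - **Only the last starters have no lag.** A reader might infer that the whole trial is extracted without any allowance. It is not: the staggered start gives earlier facilities some lag. This stands, and the point is limited accordingly.
- **The comparison between arms is largely protected.** A reader might infer that the treatment effect is biased. The article does not support that. Outcomes run to "14 months after the first visit by the GNS in the intervention arm, and for the paired facility in the control arm", and both arms are drawn from the same national data. Under-registration should therefore be similar by arm and largely cancel in the rate ratio. This stands.
- **The percentages are conditional.** Total loss over L months is a step function, and registration that builds up gradually would lose less. The window also opens at randomisation, so it can exceed 14 months and the shares may be slightly overstated. Both stand.
- **Deaths.** A reader might extend the zero lag to mortality. The sentence dates hospitalisation records only, and no date is given for the extract of deaths.
- **Paper reports.** They could flag admissions missing from the national data. The article does not describe their content, so one cannot say that they lack diagnosis codes, nor rely on them to supply codes. They are at best a partial check.
- **Loose wording.** The authors may have meant five months after the final facility completes its study period, and a full protocol may say so. That is possible. But the article fixes both the date and its purpose, the two conflict, and no other section gives a later date.

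**Conclusion.** The point holds in a limited form. On the article's own figures, the stated safeguard gives no time for late registration to the last-starting facility or facilities and their paired controls, and gives the others only their head start. The consequence is understated absolute rates and some lost precision, probably similar in both arms. It is not a demonstrated bias in the treatment comparison.

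Under total loss over an assumed three months, about 2.4% of facility-months are lost with one sequence of starts and 7% with three. Power falls from 53% to about 52% or 50%. More parallel sequences would raise the loss and gradual registration would lower it; the article does not settle either. The inconsistency should be corrected because correction is cheap, not because the result is likely to turn on it.

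**What to change.** In Outcome measures, count the five months from the end of the final pair's 14-month follow-up, which is 5 + 5 = ten months after the final facility completes its intervention. Every facility then has at least five months of lag. If the first extract cannot move, keep it, and name a refresh extract at that later time as the analysis file. Give the extract of deaths the same date.

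The cost is one changed date with results up to about five months later, to be weighed against the early-2013 date given in the Abstract, or one repeat data request.
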